## Abstract

**Background:**

Lumbar disc herniation is a common and costly problem. Moxibustion is employed to relieve symptoms and might therefore act as a therapeutic alternative. Many studies have already reported encouraging results in heat-sensitive moxibustion for lumbar disc herniation. Hence, we designed a randomized controlled clinical trial to investigate the effectiveness of heat-sensitive moxibustion compared with conventional moxibustion.

**Methods:**

This trial is a multicenter, prospective, randomized controlled clinical trial. The 316 eligible patients are randomly allocated to two different groups. The experimental group is treated with heat-sensitive moxibustion (n = 158); while the control group (n = 158) is treated with conventional moxibustion. The moxibustion locations are different for the groups. The experimental group selects heat-sensitization acupoints from the region which consists of bilateral Da Changshu (BL25) and Yao Shu (Du2). Meanwhile, fixed acupoints are used in control group; patients in both groups receive 18 sessions in 2 weeks.

**Discussion:**

The study design guarantees a high internal validity for the results. It is one large-scale randomized controlled trial to evaluate the efficacy of heat-sensitive moxibustion compared to conventional moxibustion and may provide evidence for this therapy as a treatment for moderate and severe lumbar disc herniation. Moreover, the result may uncover the inherent laws to improve the therapeutic effect with suspended moxibustion.

**Trial Registration:**

The trial is registered at Chinese Clinical Trials Registry: ChiCTR-TRC-09000604. The application date was 27 November 2009. The first patient was randomized on the 16 June 2011.

## Background

Lumbar disc herniation (LDH) is one of the most common causes of nerve root pain, and become a painful, debilitating disorder in working adults [1]. In the majority of patients, experiencing their first episode of sciatica due to LDH, the symptoms recede to a non-disabling level within a period of six weeks [2].

LDH most typical symptoms are low back pain, accompanied by one or both lower extremity pain, numbness, pain, mostly by lumbosacral, buttocks, posterolateral to the lower limbs and feet, back radiation when bending, cough worse with movements. Herniated discs also often occur without symptoms, as revealed by magnetic resonance imaging studies in asymptomatic people. They are only clinically relevant when they impinge on a nerve root, causing radiculopathy [3,4].

In general, LDH is due to disc degeneration or trauma leading to nucleus, annulus fibrosis to the vertebral canal prominent, spinal cord or nerve root compression. As a result, conventional treatments including physical therapy, pain medication, anti-inflammatory drugs and surgery, are provided by physicians. Most patients with low back pain respond well to conservative therapy [5,6]. Recently, a large number of patients with LDH are turning to complementary and alternative treatments. Complementary and alternative treatments such as acupuncture are therefore attractive. Acupuncture is often used for LDH. For example, it is gaining popularity among LDH patients in the US and about 1 million consumers with musculoskeletal disorders utilize acupuncture annually [7].

Moxibustion is a traditional Chinese method that uses the heat generated by burning herbal preparations containing Artemisia vulgaris to stimulate acupoints [8]. Moxibustion has anti-inflammatory or immunomodulatory effects against chronic inflammatory conditions in humans [9,10]. Different moxibustion methods for treatment of LDH and their mechanism may be due to moxibustion can improve local blood circulation, eliminate nerve root inflammation and edema, loosen adhesions and improve protrusion and nerve root relations or the promotion of nerve injury repair [11,12]. Moreover, the heat of moxa treatment improves microcirculation in the lumbar vertebra.

Therefore, these arthritis substances may be reduced and weakened by moxibustion. Especially for acute LDH, moxibustion may have a good effect. Severe low-back pain with leg pain (sciatica) may be caused by a herniated intervertebral disc exerting pressure on the nerve root in this stage. Nerve root inflammation and the surrounding edema aggravate the pain. The role of moxibustion may manage the pathological process.

There are many factors influencing therapeutic effect in moxibustion. But the selection of location for manipulating moxa should deserve the greatest attention [13]. Our previous studies suggested that the dominating factor in selecting the location of acupoints is associated with the area on the body surface which is affected by disease, not only the standardized fixed position [14]. In humans, acupoints contain two states: stimulated and resting. When people get sick, the acupoints on the body surface area are activated and sensitized. The sensitive areas are susceptible to heat stimulation and called "heat-sensitized acupoints". A feature of these areas is that they are specific or closely relevant to acupoints and produce the same clinical effect as "a small stimulation induces a large response". This sensitized acupoint is not only the pathological phenomenon reflecting the diseases but also an effective stimulating location with acupuncture and moxibustion [15].

Our research found that the heat-sensitive phenomenon to acupoint or an area is a new type of reaction in a pathological state [16-19]. A lot of observations and research were used to confirm this phenomenon in the 1990s [16]. We summarized the experiential evidence and found that the state of acupoints might change from the rest state to the heat-sensitized state in patients when suffering from diseases. These special acupoints might bring out further heat sensation and response in the stimulation of moxibustion heat. If we can search out these heat-sensitized acupoints associating with pathological state, good effects may be achieved. Therefore, selecting the heat-sensitized acupoint may obtain therapeutic effect far better than acupuncture and moxibustion at acupoints of the routine resting state [14]. So the heat-sensitive moxibustion is a medical technique usually involving suspended moxibustion on the heat-sensitized acupoint. A great many physicians utilized heat-sensitive moxibustion therapy in different kinds of diseases in China. Moreover, several articles and research have documented the effectiveness and safety of heat-sensitive moxibustion, such as myofascial pain syndrome [18], LDH [20], pressure sores [21] and knee osteoarthritis [22]. Together these findings suggest a superiority effect of heat-sensitized acupoints. However, the results do not provide convincing evidence. This may be because of inappropriate sample size, variability of acupuncture and sham protocols, and missing information which were frequent methodological problems [19]. Therefore, well-designed randomized controlled clinical trials are needed to establish the efficacy of heat-sensitive moxibustion for LDH.

## Method/design

### Objective

The aim of this study is to investigate the effectiveness of heat-sensitive moxibustion compared with conventional moxibustion in patients with acute LDH in China.

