### Eligibility

#### Inclusion criteria

Eligible participants will be those previously diagnosed with moderate to severe LDH, according to the M-JOA criteria(> 10 score). Patients will be required to complete the baseline LDH diary. Written informed consent will be obtained from each participant. Participants 18 to 65 years of age will be recruited from outpatient and inpatient in four centers. Standard of diagnosis listed as follows:

① Pain occurred in lower back and radiated to the lower limb; ② Limitations of tender point; ③ Straight leg raising test and it's strengthen test are positive; ④ Skin sensation, muscle strength and tendon reflex have some changes; Changes in spinal posture; ⑤ CT suggestive of disc herniation. The above standard mainly originated from the guiding principle of clinical research on new drugs (GPCRND) [23]. Since the research involves moderate to severe LDH or severe LDH, the inclusion criteria will restrict the following conditions: According to the below LDH diagnosis standard, meanwhile, the triangle region formed with bilateral Da Changshu (BL 25)and Yao Shu (Du 2) of patients (Da Changshu- Yao Shu -contralateral Da Changshu intra-region) appear heat-sensitive points.

Participants will be instructed to stop LDH symptomatic relief medication during the run-in and treatment periods and will be provided the usual care instruction for LDH.

Figure 1 The flow diagram is intended to depict the passage of participants through this RCT.

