#### Exclusion criteria

Participants will be excluded if they suffer from serious life-threatening disease, such as disease of the heart and brain, blood, vessels, liver, kidney and hematopoietic system, and psychotic patients. Participants will not be eligible if they are female and whether pregnant or lactating. The following conditions

are also excluded items: appeared a single nerve palsy, or cauda equina nerve palsy, manifested as muscle paralysis or have rectum or bladder problems; complicated with lumbar spinal canal stenosis and space-occupying lesions or for other reasons; complicated with lumbar spine tumors, infections, tuberculosis; moxibustion syncope and unwilling to be treated with moxibustion; do not sign informed consent.

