#### Baseline data

Baseline characteristics will be shown as mean, standard deviation (SD) for continuous data including age, previous duration, and so on. The first step of analysis is to check for integrity of randomization. The unbalanced analysis in baseline characteristics will use ANCOVA.

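### The objective is about acute LDH, but eligibility sets no limit on symptom duration and requires heat-sensitive points, so the objective and conclusion do not name the population enrolled

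*Protocol article*

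**What the plan says.** The Objective section gives the aim as studying "the effectiveness of heat-sensitive moxibustion compared with conventional moxibustion in patients with acute LDH in China". *Acute* is the only disease qualifier in that sentence.

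The Inclusion criteria section defines the patients differently: "Eligible participants will be those previously diagnosed with moderate to severe LDH, according to the M-JOA criteria(> 10 score". On age and setting it says: "Participants 18 to 65 years of age will be recruited from outpatient and inpatient in four centers". It lists five diagnostic items (radiating pain, tender points, straight leg raising, neurological or postural change, CT) and then adds a requirement about the triangle between the two BL25 points and Du2: "Da Changshu- Yao Shu -contralateral Da Changshu intra-region) appear heat-sensitive points".

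The Exclusion criteria section removes serious systemic disease, pregnancy and lactation, nerve palsy, spinal tumour or infection, and cases "complicated with lumbar spinal canal stenosis and space-occupying lesions or for other reasons". Long-standing or recurrent LDH is not on the list.

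The Baseline data section will summarise "continuous data including age, previous duration, and so on". This is the only place where duration of illness appears as a trial variable.

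The Discussion paragraph of the abstract says that the trial "may provide evidence for this therapy as a treatment for moderate and severe lumbar disc herniation". It mentions neither acute disease nor heat-sensitive points.

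**The concern.** The target population is described in three ways: acute LDH in the objective, moderate and severe LDH in the abstract, and moderate to severe LDH of any duration with heat-sensitive points in the criteria. Only the last describes who can be randomised.

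Duration is not an incidental feature of this disease. The Background says that for most patients with a first episode of sciatica from LDH, symptoms fall to a non-disabling level within six weeks. Recent-onset and long-standing disease may therefore follow different courses over a six-month follow-up. If the objective is carried into the results paper unchanged, readers will take a mixed-duration result as evidence about acute LDH. If the abstract's wording is carried over, they will apply it to patients without heat-sensitive points, none of whom could enter the trial.

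**Working it through.** This point needs no arithmetic. The plan's one related figure reproduces and is not in question: 126 / (1 − 0.20) = 157.5, rounded up to 158 per group, and 2 × 158 = 316. The check is a comparison of sections.

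| Section | Acuteness or duration | Heat-sensitive points |
|---|---|---|
| Objective | acute LDH | not mentioned |
| Abstract, Discussion | not mentioned | not mentioned |
| Inclusion criteria | no limit, no definition | required |
| Exclusion criteria | chronic disease not excluded | not mentioned |
| Baseline data | duration summarised only | not mentioned |

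**Step 1. Does any listed criterion stand in for acuteness?** The entry threshold is an M-JOA score above 10. Table 1 has ten items: pain, numbness, tenderness, muscle power, straight leg raising, radiating pain, stooping and lifting, walking, daily time in bed, and ability to work. All grade present severity or function; none asks about onset. The five diagnostic items are signs and imaging, and a patient with long-standing disease can meet all of them. A previous diagnosis is required, with no statement of how recent it must be.

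**Step 2. Does the analysis isolate the acute patients?** No. The Outcome data section names the baseline score as covariate, treatment as fixed factor and subject as random effect. The Baseline data section appears to keep ANCOVA for characteristics found unbalanced, so duration would enter only if an imbalance were seen. No acute subset is defined. I take previous duration there to mean duration of the LDH illness, since the section does not define it.

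**Step 3. What population results?** Applying the listed criteria gives patients aged 18 to 65 with moderate to severe LDH, of any duration, who show heat-sensitive points in the stated region. Acute patients may enter but are not separated from the others. Their share is not given and, on the criteria alone, can lie anywhere from 0 to 100%.

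**Step 4. Does the heat-sensitive-point criterion affect the comparison?** It is an entry condition met before randomisation by both arms, so the randomised contrast stays fair. It restricts the population to which the contrast refers. The proportion of LDH patients who meet it is not stated.

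**The case against.** The best reply has four parts.

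*The abstract's conclusion already fits the criteria.* It speaks of moderate and severe disease, which is what an M-JOA score above 10 selects, and acute patients are not shut out. This stands: the acute mismatch lies between the objective and eligibility, and the abstract is at fault only for omitting the heat-sensitive-point restriction.

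*Acute may be meant clinically.* The Background describes the acute stage as severe back and leg pain with nerve root inflammation, and the signs required at entry may be the authors' working version of it. That is possible, but the document does not say so, and the signs do not separate recent from long-standing disease. On this reading a definition is missing, and the wording still has to be reconciled.

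*The article condenses a fuller protocol.* It does, but it sets out eligibility in detail, and the only qualifier in its objective has no counterpart there. If the full protocol carries a duration limit, the article should state it.

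*The heat-sensitive-point criterion is openly stated and inherent to the question.* The experimental technique cannot be delivered without such a point, and objectives do not normally repeat every criterion. This stands as far as bias is concerned. A reader might infer that the criterion favours the experimental arm, but the document does not support that: controls meet the same criterion, BL25 is among their treatment points, and the article says that heat-sensitisation is neither sought nor avoided in them. What remains is a limit on generalisability, which a conclusion about moderate and severe LDH at large should carry.

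**Conclusion.** The point holds as a mismatch between stated elements of the plan. The objective names acute LDH; the criteria admit any duration and require heat-sensitive points. A result from this sample cannot be reported as a finding for acute LDH, nor without qualification for moderate and severe LDH in general. Internal validity, the randomisation and the sample size are unaffected. It should be corrected before analysis because it changes what the trial may claim. The verdict assumes that the eligibility criteria in the article are complete as regards duration.

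A reader might go further and infer that patients with long-standing disease will dilute the effect and cost power. The documents do not support this. The Background remark that acute disease may respond especially well concerns moxibustion in general, which both arms receive, and *especially* does not mean *only*. The argument for heat-sensitised over fixed points rests on illness sensitising acupoints and does not refer to acuteness. The Sample size section gives no effect size or SD, and no acute share is stated, so a power loss could be computed only from invented inputs.

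**What to change.** 1. Reconcile the Objective, the Inclusion criteria and the abstract's Discussion so that all three name one population. Which one was intended is for the investigators to say. The first patient was randomised on 16 June 2011, so the cheap route is to describe the patients being enrolled: remove *acute* and refer to patients with moderate to severe LDH who show heat-sensitive points in the BL25–Du2 region.
2. Put baseline symptom duration into the primary model as a covariate, in a form fixed before unblinding, whether or not the groups differ on it. This accounts for a likely prognostic factor; it does not turn the overall estimate into one for acute disease.
3. Optionally, report a treatment-by-duration analysis, labelled exploratory. The trial is not sized for an interaction.

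The cost is a few changed sentences and one covariate that is already collected. Treatment, randomisation, the primary outcome and the sample size stay as they are. The claim becomes narrower and matches the patients studied.

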### Outcome

The improvement Japanese Orthopedic Association has proposed a series of criteria to define patient response in the context of clinical trials of LDH. M-JOA scale is known as the modified edition of JOA Back Pain Evaluation Questionnaire [23]. According to these criteria, a patient with LDH is assessed including pain, the activities of daily life and work, function impairment, and special exams (Table 1). This scoring system was previously validated [23]. The degree of LDH is divided into three levels: mild: < 10, moderate: 10 to 20, severe: > 20.

**Table 1 T1:** List of M-JOA

Item	Grade/Classification	Score
Subjective symptoms		
Lumbar and leg pain	No	0
	Mild pain or occasional moderate pain	1
	Usual moderate pain or occasional severe pain	2
	Frequent or continuous severe pain	3
Numbness	No	0
	Occasional	1
	Frequent but relief may be on their own	2
	Continuous, not alleviated	3
Objective signs		
Paravertebral tenderness	No	0
	Mild	1
	Moderate	2
	Severe	3
Myodynamia	Grade V	3
	Grade IV	2
	Grade III	1
	Grade 0 to II	0
Straight let raising test	> 70°, straight leg drive up (-)	0
	> 45°, straight leg drive up (+)	1
	> 30°, straight leg drive up (+)	2
	< 30°, straight leg drive up (+)	3
Radiating pain	No	0
	Hip/thigh	1
	Shank	2
	Foot	3
Activities of daily life and work		
Stoop and lift heavy things	Normal stoop, lift weight > 3 kg	0
	Able to stoop, lift weight ≤ 3 kg	1
	Unable to stoop	2
	Serious difficulties in bending and lifting	3
Walking distance/time	Walking ≥ 1 km or 60 min	0
	Walking ≥ 500 m or 30 min	1
	Walking ≥ 100 m or 10 min	2
	Serious difficulties in walking	3
Daily time in bed(h)	< 10	0
	10 to 12	1
	12 to 16	2
	> 16	3
Ability to work	Full-time to do as before	0
	Although able to work, occasionally need a break	1
	Although able to work, usually need a break	2
	Unable to work	3

Therapeutic effect is assessed by comparing baseline and final conditions reported by the patient. This trial also records adverse effects reported by patients during treatment. The outcome measures above will be assessed before treatment, the 14 days after the last moxibustion session and 6 months after the last moxibustion session.

To evaluate the improvement of severity, we will make use of M-JOA score and take the secondary analysis. Improvement rate = [(scores before treatment - after treatment score)/pretreatment score] × 100%. Definition are listed below: Clinically important improvement as ≥ 75%, markedly effective improvement as 50 to 75%, improved as 30 to 50% and ineffective as < 30%. The numbers in the four categories will be calculated respectively at every time point.

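### The muscle-strength item of the M-JOA is printed in the opposite direction to the other nine items, so summing the table as it stands counts recovery of strength as worsening

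*Protocol article*

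**What the plan says.** Table 1 of the Protocol article (Outcome) lists ten items, each scored 0 to 3.

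- **Muscle strength:** the row opens with "Myodynamia Grade V 3". Grade IV then scores 2, Grade III scores 1 and Grade 0 to II scores 0.
- **Other items:** pain is typical, running from "Lumbar and leg pain No 0" to "Frequent or continuous severe pain 3". The work item ends at "Unable to work 3".
- **Direction of the total:** the bands are "mild: < 10, moderate: 10 to 20, severe: > 20", so higher is worse. The improvement rate is the score before treatment minus the score after, divided by the score before, so a fall is improvement. It is cut into categories: "Clinically important improvement as ≥ 75%, markedly effective improvement as 50 to 75%, improved as 30 to 50% and ineffective as < 30".
- **Uses of the total:** Follow-up data names the M-JOA score as the primary outcome, compared between groups at 14 days. Inclusion criteria admits patients "according to the M-JOA criteria(> 10 score".
- **Muscle strength in this population:** changed strength is among the diagnostic signs in Inclusion criteria. Exclusion criteria removes patients with nerve palsy showing as muscle paralysis.

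**The concern.** A severity score works only if every item points the same way. Here one item of ten rewards weakness and penalises strength, while the bands and the improvement formula assume that it does the reverse. The article nowhere says that the item is subtracted or recoded before the total is formed. This is a contradiction within the definition of the primary outcome, not a detail left to a later analysis plan.

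Three uses of the score would be affected if centres or analysts follow the table:

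- In a patient whose strength recovers, the item offsets improvement on the other items.
- The improvement rate has the wrong numerator in patients whose strength grade changes and the wrong denominator in all patients, so patients can fall into the wrong response category.
- Full strength adds 3 points towards the entry threshold, and marked weakness adds none.

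**Working it through.** **Inputs.** All come from the Outcome section (Table 1, severity bands, improvement formula) and Inclusion criteria (entry above 10). One assumption is needed: the total is the plain sum of the ten items. The article does not say so, but ten items scored 0 to 3 and bands running past 20 imply it.

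**Notation.** S is the sum of the other nine items (0 to 27) and g is the printed strength score (Grade V = 3, IV = 2, III = 1, 0 to II = 0). Then:

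- printed total = S + g
- consistent total = S + (3 - g)
- printed minus consistent = 2g - 3, which is +3 at Grade V, +1 at IV, -1 at III and -3 at 0 to II.

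**Ends of the scale.** Normal on every item: printed 0 + 3 = 3, consistent 0. Worst level on every item: printed 27 + 0 = 27, consistent 27 + 3 = 30. As printed, a total of 30 requires full strength.

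**Change within a patient.** Improvement rate = (before - after)/before.

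| Other nine items | Strength | Printed total | Printed rate | Consistent total | Consistent rate |
|---|---|---|---|---|---|
| 12 to 12 | III to V | 13 to 15 | (13-15)/13 = -15.4% | 14 to 12 | (14-12)/14 = +14.3% |
| 14 to 4 | III to V | 15 to 7 | (15-7)/15 = 53.3% | 16 to 4 | (16-4)/16 = 75.0% |

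The second patient falls from the top response category to the next one down.

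**Complete recovery.** A patient who ends normal on every item has a printed total of 3, so the rate is (b - 3)/b from a printed baseline b:

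- b = 11: 8/11 = 72.7%, below the 75% cut
- b = 12: 9/12 = 75.0%
- b = 15: 12/15 = 80.0%.

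A patient who enters at 11 and ends normal except for Grade IV strength has a printed total of 2, and (11 - 2)/11 = 81.8%. Residual weakness therefore gives a better result than full recovery.

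**Entry.** With S = 8 and Grade V, the consistent total is 8 and the printed total is 11, which passes the threshold. With S = 9 and Grade III, the consistent total is 9 + 2 = 11 and the printed total is 9 + 1 = 10, which does not pass.

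**Primary comparison.** Since printed minus consistent is 2g - 3, the printed difference in 14-day means equals the consistent difference plus twice the group difference in mean g. Patients at Grade V throughout carry a constant 3 and contribute no distortion to that difference. The article gives no distribution of strength grades and no item effects.

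**Power.** Sample size gives 126 per group before dropout, and 126/0.80 = 157.5, rounded up to 158, reproduces its final figure. It states no effect size or SD. The 126 corresponds to a standardised difference of (1.960 + 1.282) × √(2/126) = 0.408, but nothing divides that difference among the items.

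**The case against.** **It may be a misprint.** The article says the scale comes from a cited source and was previously validated. Neither that source nor the case report form is shown, and the table has other slips. In the stooping item, for example, inability to stoop scores 2 and serious difficulty scores 3. If only the printed row is wrong, patients were scored correctly. This stands: a reader might infer that eligibility and outcome data are already corrupted, and the article does not show that. The stooping oddity concerns two adjacent levels and does not reverse that item's overall direction.

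**Loss of power is not shown.** A reader might infer that the stated 90% power falls substantially. Assume unit item variances, a common correlation ρ and an equal effect on all ten items. The effect then drops from 10 units to 9 - 1 = 8, and the variance from 10 + 90ρ to 10 + 54ρ. Starting from 0.408, power is about 74% at ρ = 0, 82% at ρ = 0.1 and 87% at ρ = 0.3. The equal effect is the decisive assumption, and the article gives no support for it. With no effect on strength, the same model gives 95% at ρ = 0.1 and 97% at ρ = 0.3, because the reversed item also lowers the variance. The printed score has more power than the consistent one once the strength effect is below about 0.47 (ρ = 0.1) or 0.77 (ρ = 0.3) of the others. Even the direction is undetermined, so no power figure should be claimed.

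**The ceiling is narrow.** It is tempting to say that a patient entering at 11 can never reach the top category. That is false, as the Grade IV case above shows. Among patients who recover fully, and with entry above 10, only a baseline of 11 is blocked. The improvement rate also belongs to the secondary analysis.

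**Severe weakness may be rare.** The exclusion of palsy with muscle paralysis plausibly removes many patients at Grade 0 to II, so examples at that extreme may describe people who would not be enrolled. This stands, but Grades III to V remain and the reversal affects them.

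None of this reconciles the row with the bands, the formula or the other items.

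**Conclusion.** The point holds as an internal contradiction in the definition of the primary outcome, and it must be corrected. As printed, one item of ten runs against the rest and shifts a patient's total by +3, +1, -1 or -3 points according to strength grade, on a scale of 30 with entry above 10. It reverses the sign of any change in strength and can move patients across the entry threshold and the response categories.

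These figures rest on the total being a plain sum and on the table being applied as printed; the article implies the first and cannot settle the second. The effect on the primary group difference and on power is unquantified. It depends on how many patients change strength grade and whether that differs between groups, neither of which is given.

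**What to change.** 1. Check the muscle-strength row against the source scale, the case report form and the scoring program, to learn whether the printed scoring was used.
2. Correct the row so that it runs with the other items: Grade V = 0, Grade IV = 1, Grade III = 2, Grade 0 to II = 3.
3. If the printed scoring was used, recompute baseline and follow-up totals, and the improvement rates, from the recorded item grades. Keep every randomised patient in the intention-to-treat analysis that the Statistical analysis plan section promises. Report how many would have missed the entry threshold under consistent scoring, and do not remove them.
4. Separately, reconcile the moderate band, which includes a total of exactly 10, with the inclusion criterion, which requires more than 10.

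The cost is one table row, a check of the case report form and, if needed, a programmed re-score. No new data are needed if item grades were recorded. Re-scoring cannot recover patients wrongly refused entry, and Trial Registration gives a first randomisation in June 2011, so the check should be made promptly.

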##### Follow-up data

The primary outcome will be the M-JOA scores. The primary analysis will compare the two groups at 14 days. A secondary analysis will compare the two groups at 6 months to assess if any differences between groups have been maintained over time.

Loss to follow-up is likely to lead to biased estimates of intervention effect. We will try to avoid bias due to attrition by carefully following up the participants in both groups. We will phone participants who do not complete questionnaires after a second reminder. We anticipate a 20% loss to follow-up in this trial, and will implement procedures to minimize loss to follow-up and patient withdrawal, and where possible we will collect information on reasons for patient withdrawal.

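### Grades 2 and 3 of the stoop-and-lift item in the primary outcome (M-JOA) overlap and appear out of order as printed

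*Protocol article*

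**What the plan says.** The Follow-up data section states "The primary outcome will be the M-JOA scores" and "The primary analysis will compare the two groups at 14 days". The Outcome section fixes the direction of the scale: "The degree of LDH is divided into three levels: mild: < 10, moderate: 10 to 20, severe: > 20". The improvement rate in the same section is the fall in score divided by the pretreatment score, so a fall counts as benefit.

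Table 1 prints the stoop-and-lift item as follows:

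- 0: "Normal stoop, lift weight > 3 kg"
- 1: "Able to stoop, lift weight ≤ 3 kg"
- 2: "Unable to stoop"
- 3: "Serious difficulties in bending and lifting"

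In the same block of the table, "Unable to work" takes the worst grade, 3. The walking item also ends at 3, but its worst grade is labelled as serious difficulty, not inability. Nothing else in the article explains or corrects the order of the stoop item.

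**The concern.** Read literally, complete inability to stoop scores one point better than serious difficulty with bending. The work item in the same block treats inability as the worst state, so the table does not handle inability in one consistent way. The two grades are also not exclusive, because someone who cannot stoop plainly has serious difficulty bending.

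Two things are at stake. A genuine improvement between these states can be recorded as a worsening of the item. Assessors can also grade the same patient differently, and the Design section has four centres contributing ratings. Both feed the total that the primary analysis compares, and the responder categories built from it.

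**Working it through.** **Inputs.** The item codes, the direction of the scale and the improvement formula come from the Outcome section. Table 1 has ten items scored 0 to 3, so the total runs from 0 to 10 × 3 = 30. One assumption is added for the comparison column below: in a severity-ordered item, inability ranks worse than serious difficulty (3 against 2).

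**Step 1: item change under each coding.**

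| Change in patient | Printed codes | Severity-ordered codes | Printed minus ordered |
|---|---|---|---|
| Unable → serious difficulty | 3 − 2 = +1 | 2 − 3 = −1 | +2 |
| Unable → grade 1 | 1 − 2 = −1 | 1 − 3 = −2 | +1 |
| Unable → grade 0 | 0 − 2 = −2 | 0 − 3 = −3 | +1 |
| Serious difficulty → grade 1 | 1 − 3 = −2 | 1 − 2 = −1 | −1 |
| Serious difficulty → grade 0 | 0 − 3 = −3 | 0 − 2 = −2 | −1 |

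The full 2-point swing arises only for a move between the two disputed grades. Other moves out of those grades are off by 1 point. Gains by patients who start unable are understated, and gains by those who start with serious difficulty are overstated.

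**Step 2: effect on the improvement rate.** One point is worth 1/baseline: 1/11 = 9.1 percentage points at a baseline of 11, 1/20 = 5.0 at 20, and 1/30 = 3.3 at 30.

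**Step 3: illustration (assumed values).** Take a printed baseline of 20 with this item at unable. The other nine items fall by 6, and this item moves to serious difficulty.

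- Printed: after = 20 − 6 + 1 = 15; improvement = 5/20 = 25%, below the 30% cut-off, hence ineffective.
- Severity-ordered: baseline = 21; after = 21 − 6 − 1 = 14; improvement = 7/21 = 33%, hence improved.

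The patient's state is the same, but the category differs.

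**Step 4: overlap.** A patient who cannot stoop satisfies the words of grade 2 and, in ordinary English, those of grade 3. The walking item does not have this problem, because its grade 2 is a measured distance or time.

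**Step 5: group level.** If the two grades are swapped, the printed mean difference at the primary time point departs from the ordered one by the between-arm difference in the proportion with serious difficulty, minus the between-arm difference in the proportion unable. The documents give neither proportion, so no value follows.

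The Sample size section does not help to scale the effect. Its inflation for loss to follow-up reproduces (126/0.8 = 157.5, rounded up to 158 per group), but the article states no target difference or SD in M-JOA points.

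**The case against.** The strongest reply is that the order may be right and only the wording poor. The item covers two functions. Grade 2 names stooping alone and grade 3 names both bending and lifting, so grade 3 could mean that both are seriously impaired. On that reading the codes run correctly, and swapping them would create an error. The walking item supports this, since there too serious difficulty is the label of the worst grade. The English in the table is rough in other places, the trial runs at four centres in China, and the Outcome section says the scoring system was validated previously. The raters' form may therefore be sound.

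Much of this stands. A reader might infer from Table 1 that the item is certainly reversed. The document shows only that the grades appear out of order, and the source scale that would settle it is not available here. The reply does not rescue the printed item, however. Even on the two-function reading, a patient who cannot stoop can be placed in grade 2 or grade 3, and validation of the source does not vouch for the wording printed here.

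It is also fair that this is one item of ten. A patient's total changes sign only if the other nine items net to almost nothing. Enrolment covers moderate to severe disease (score above 10), and a patient can qualify without reaching grade 2 or 3 on this item.

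**Conclusion.** The point holds as a fault in a stated scoring rule of the primary outcome. As printed, grades 2 and 3 overlap and appear misordered. For an affected patient the error is at most 2 points on a 0 to 30 total, and 1 point for other moves out of these grades. That is enough to shift some patients across an improvement-rate cut-off. These sizes rest on the assumption that inability is the worse state. The overlap does not depend on that assumption.

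A reader might go further and infer that the treatment comparison is biased by some definite fraction of the detectable difference. The documents do not support that. They give no distribution over these grades, no SD and no target difference, and any figure would rest on an assumed imbalance between arms. The same item is applied in both arms, allocation is random and assessors are described as blinded. The expected consequence is therefore mainly noise in the M-JOA comparison and misclassified individual change, not demonstrated bias between arms. A correction should be made, but the fault does not undermine the design.

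**What to change.** Reconcile the item with the source scale and with the case report form in use before changing any code.

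- If the form is right and only the printed table is wrong, correct the table.
- If the form carries the same wording, reword the four levels so that they are ordered and mutually exclusive, and introduce the corrected form at all four centres together. Re-code completed forms only where the recorded level is unambiguous. State that ambiguous past ratings cannot be fully recovered, because re-coding cannot undo inconsistent choices between overlapping levels. This may matter, since the abstract reports a first randomization in June 2011.

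In the same revision, settle two boundaries in Table 1: 12 hours in bed falls in both grade 1 and grade 2, and a straight-leg raise of exactly 30° falls in no grade.

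The cost is low: a check against the source, a correction to the table or form, and re-coding of one item where possible. The sample size does not change.
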